## Abstract

**Background:**

Frailty in elderly patients is associated with an increased risk of poor health outcomes, including falls, delirium, malnutrition, hospitalisation, and mortality. Because polypharmacy is recognised as a possible major contributor to the pathogenesis of geriatric frailty, reducing inappropriate medication exposure is supposed to be a promising approach to improve health-related quality of life and prevent adverse outcomes. A major challenge for the process of deprescribing of inappropriate polypharmacy is to improve the communication between general practitioner (GPs), patient and family carer. This study investigates the effects of a complex intervention in frail elderly patients with polypharmacy living at home.

**Methods:**

This is a cluster randomised controlled trial including 136 GPs and 676 patients. Patients with a positive clinical screening for frailty are eligible if they are aged 70 years or older, receiving family or professional nursing care at home, and taking in five or more drugs per day. Exclusion criteria are higher grade of dementia and life expectancy of 6 months or less. The GPs of the intervention group receive an educational training promoting a deprescribing guideline and providing information on how to conduct a family conference focussing on prioritisation of treatment goals concerning drug therapy. During the 1-year intervention, GPs are expected to perform a total of three family conferences, each including a structured medication review with patients and their family carers. GPs of the control group will receive no training and will deliver care as usual. Geriatric assessment of all patients will be performed by study nurses during home visits at baseline and after 6 and 12 months. The primary outcome is the hospitalisation rate during the observation period of 12 months. Secondary outcomes are number and appropriateness of medications, mobility, weakness, cognition, depressive disorder, health-related quality of life, activities of daily living, weight, and costs of health care use.

**Discussion:**

This study will provide evidence for a pragmatic co-operative and patient-centred educational intervention using family conferences to improve patient safety in frail elderly patients with polypharmacy.

**Trial registration:**

German Clinical Trials Register, DRKS00015055 (WHO International Clinical Trials Registry Platform [ICTRP]). Registered on 6 February 2019.

## Background

Frailty in elderly patients is a vulnerable health status characterised by an increased risk of adverse health outcomes and/or dying when exposed to a stressor [1, 2]. Physical frailty is defined as a clinical syndrome or multidimensional risk state often associated with weight loss, sarcopenia, weakness, exhaustion, and reduced physical activity [3, 4]. Frailty is associated with an increased risk of poor health outcomes, including falls, delirium, malnutrition, hospitalisation, and mortality [1, 5]. However, geriatric frailty is not a categorical irreversible status; it can be addressed by various interventions [6, 7].

Polypharmacy is recognised as a possible major contributor to the pathogenesis of frailty [8]. Despite the undisputable benefit of drug treatment for certain conditions, a large number of medications in patients with multimorbidity increases the risk of adverse drug reactions (ADRs) due to age-related changes in pharmacokinetics, pharmacodynamics, and physiology (resulting in higher sensitivity), as well as due to drug interactions [9, 10]. ADRs are found in 35% of older people cared for at home [11]. It has been assumed that 2.4–6.5% of all hospital admissions are drug related. In older people, these figures are considerably higher [12–14]. Polypharmacy independently increases the risk of falling, frailty, hospital admission [15–17], and mortality [18]. Excessive polypharmacy (ten or more drugs) is an independent risk factor for death in vulnerable geriatric patients [18]. Reducing inappropriate medication exposure in frail patients is supposed to be a promising approach to improve health-related quality of life and prevent adverse outcomes [19–21].

Only very few randomised controlled trials have been conducted to investigate the outcomes of medication tapering or withdrawal of single drugs such as antihypertensives, statins, or benzodiazepines [22]. Particularly, the reduction of psychotropic drugs can often be realised with beneficial effects for patients [23]. In frail patients, drug treatment aimed at prolonging life (e.g., cardiovascular disease prevention) is often a less important therapeutic goal due to limited overall life expectancy [18], and a significant proportion of older adults is willing to reduce their number of daily drugs [24].

Selecting appropriate patients on the basis of fully informed consent from patients and carers and taking a palliative care perspective with the intention to reduce polypharmacy has been shown to be a successful process for improving older persons’ quality of life [25]. A recent review summarised the effects of interventions on optimising polypharmacy in older people and found that most of the interventions were aimed at optimising surrogate outcomes such as number of drugs and number of inappropriate medications. However, the impact on patient-relevant outcomes has not been properly studied yet [26].

Many barriers to deprescribing inappropriate polypharmacy have been identified in physicians, patients, and relatives, resulting in major challenges to the communication process between the participating actors [24, 27]. Therefore, interventions to reduce polypharmacy should be embedded in a shared decision-making process of general practitioners (GPs), patients, and family carers [28]. Family carers play a pivotal role in daily drug management, such as by avoiding failure to receive drugs, paying attention to ADRs, and supporting patient adherence [29].

Family conferences are a well-established instrument in nursing, intensive care units, and palliative care [30, 31]. Family conferences are a forum for communication between patients, physicians, nursing staff, and family members [31–33]. From the families’ point of view, treatment changes for a chronic illness are among the three major indications for a family conference with a GP (apart from terminal illness and hospitalisation). Although family conferences are effective in improving the communication process [31] and involvement of frail patients in planning conferences is possible [34], up to now, no intervention study has investigated their effects on polypharmacy in frail patients cared for at home.

This study evaluates the effects of a complex intervention including repeated structured medication reviews and family conferences in frail elderly patients with polypharmacy living at home. The primary hypothesis is that patient safety operationalised as the hospitalisation rate will be reduced in the intervention group compared with the control group with usual care within the study period of 12 months. Secondary hypotheses include that the intervention will reduce the number of prescribed inappropriate drugs, improve health-related quality of life, reduce the rate of falls, and reduce the rate of emergency services. Additionally, we expect that in the intervention group, self-determination of patients will improve and the process of shared decision making between GPs, patients, and family carers will be enhanced.

### Study setting and participants

This study will be performed in a primary care setting in two areas of Germany (Düsseldorf and Rostock). At first, 136 GPs will be recruited. The GPs will be requested to enrol 676 frail elderly patients (average of 5 patients per GP) with polypharmacy living at home (Fig. 1). Patients are eligible to participate in the study if they meet all of the following criteria:
Positive screening of frailty in a short screening questionnaire answered by their GP using the Canadian Study of Health and Aging Clinical Frailty Scale [5]. Patients at levels 5–7 are eligible to participate in this trial.Aged 70 years or olderRegular intake of five or more different drugs per day (defined as polypharmacy)Care dependency (need for care assessed by the medical service of the German long-term care insurance) or comparable statusReceiving nursing care in the domestic environment, provided either by informal family carers alone or by professional ambulatory care services

**Fig. 1 Fig1:**
[figure not shown]
Family Conferences and Shared Prioritization to Improve Patient Safety in the Frail Elderly (COFRAIL) study flow chart

Patients are not eligible to participate in the study if they meet one or more of the following criteria as rated by their GPs:
Moderate or severe dementiaBeing under legal guardianshipReduced life expectancy of 6 months or less (palliative care)Living in a nursing homeInsufficient German-language skills of patients and/or family carer and no translator available

### Recruitment and incentives

The study centres will send an invitation letter to the local GPs with a request to answer by email or fax if interested in participating in the study. In the next step, the GPs will be contacted by the study staff in order to hand out further information and to get informed consent of the GPs. In addition, some local information events on the topic of geriatric frailty syndrome will be offered to all interested GPs without disclosing the study objective, which is deprescribing. Each of the enrolled GPs is requested to include five eligible patients in the study.

Participating GPs in both the intervention group and the control group receive an expense allowance for every enrolled patient of €100. Patients and carers will not receive financial incentives for participating in the study.

### Intervention

#### Experimental intervention

In the first phase of the Family Conferences and Shared Prioritisation to Improve Patient Safety in the Frail Elderly (COFRAIL) study, a systematic process of intervention development was conducted with collaboration of all project partners. The feasibility of the recruitment process and the COFRAIL intervention was tested in a pilot study. For this purpose, four GPs conducted eight family conferences with frail elderly patients and at least one family member. For evaluation purposes, the GPs and the family carers were interviewed by telephone after the family conferences. Conclusions from the pilot study regarding the educational concept will be drawn by consulting all project partners.

The experimental intervention will be performed in two steps:
*Step 1*: GPs allocated to the intervention arm will receive an educational intervention covering the following topics: (a) structured patient-centred medication review, (b) family conference according to a structured guideline with special focus on prioritisation of treatment goals concerning drug therapy (communication training included), and (c) structured deprescribing protocol in case of a decision in favour of reducing the drug burden. Over the course of the trial, altogether three trainings (two meetings in the first year and one optional meeting in the second year) are required to achieve the educational objectives and to enhance the safety of the intervention by giving the GPs the opportunity to discuss their experiences with colleagues based on their own cases. An overview of the educational intervention programme is presented in Fig. 2.*Step 2*: During the 1-year intervention, GPs will perform a total of three family conferences per enrolled patient each, including a structured medication review with the enrolled patient and the patient’s family carer instead of routine home visits or consultations. The family conferences are scheduled at the beginning of the study, after 3 months, and after 9 months, each lasting about 30–45 min. The conversations will initially focus on the medications taken by the patient (brown bag review), followed by a discussion about treatment goals and priorities of the patient and the family carers. The family conferences can be conducted optionally in the doctor’s office or at the patient’s home. If desired by the team and/or physician, counselling by an external clinical pharmacologist/pharmacist will be provided via phone or email.

**Fig. 2 Fig2:**
[figure not shown]
Elements of the educational intervention

If both patient and physician in agreement consider reducing polypharmacy, the GP is recommended to follow a structured deprescribing protocol based on those published by Scott [25] and Garfinkel [20], including five steps: (1) ascertain all drugs the patient is currently taking and the reasons for each one, (2) consider overall risk of drug-induced harm in individual patients to determine the required intensity of deprescribing intervention, (3) assess each drug in regard to its current or future benefit compared with current or future harm or potential burden, (4) prioritise drugs for discontinuation that have the lowest benefit-to-harm ratio and lowest likelihood of adverse withdrawal reactions or disease rebound syndromes, and (5) implement a discontinuation regime and monitor patients closely for improvement in outcomes or onset of adverse effects.

In addition, the GP has the option to obtain a written medication review for the patient by a clinical pharmacologist associated with the study group.

There will be no special criteria for discontinuing or modifying allocated interventions. Implementing training and up to three family conferences may alter usual care pathways (including use of any medication) in GP practices randomised to the intervention.

There is no anticipated harm and no compensation for trial participation. It is not necessary to provide post-trial care.

#### Control group

Patients in the control group will receive care as usual. GPs in the control group will be offered training seminars on clinical topics for daily practice that do not interfere with the intervention.

At the end of the observational period, the educational intervention will be offered to GPs in the control group due to motivational reasons. This offer will not influence study outcomes but should maintain the motivation of the GPs assigned randomly to the control arm.

### Measurements

At the beginning of the trial, the following parameters will be collected on the GP’s level by a self-administered questionnaire: age, sex, number of practicing GPs in the practice, number of treatment cases per year, year of licensure to practice medicine, and board-certified specialities. The GPs will be requested to provide the following data of patients from the patients’ medical records at baseline: chronic diagnoses and medication schedule. After 6 and 12 months, new chronic diagnoses and medication schedules shall be reported. This trial does not involve collecting biological specimens.

A geriatric assessment of patients will be performed by trained study nurses during home visits at baseline, after 6 months (T_1_), and after 12 months (T_2_). The following sociodemographic parameters of patients will be recorded by study nurses: age, sex, level of education, marital status, household members, degree of disability (*Grad der Behinderung*), level of care dependency assessed by the medical service of the German social care insurance (*Pflegegrad*). In addition, the study nurse will collect data on all medications used by the patient within the last week. The data include product name, pharmaceutical form, content of the active substance, German national drug code, periodic or as needed (*pro re nata*) medication, dosage and frequency (for periodic medication), and duration of prescription (less than 1 week, 1 week or longer but less than 1 month, 1 month or longer but less than 2 months, 2 months or longer but less than 6 months, 6 months or longer but less than 1 year, or 1 year or longer). The interviewer will ask the patient to show the packages of the pharmaceuticals to get the most valid information.

The patients will be requested to keep an event diary to document number of falls, weight, hospitalisations, and any other health care use which is further explained below under the heading ‘Additional health economic parameters’. The event diary will be handed over, collected, and validated by the study nurses during their home visits.

#### Primary outcome

The primary endpoint of the study is the number of hospitalisations per patient during the observation period of 12 months. This outcome does not include visits to an outpatient clinic or visits to an emergency unit without hospital admission. The hospitalisations will be documented by the participating GPs after 6 and 12 months and by the patients in their event diary. In case of disparity between the number of hospitalisations documented by GPs and patients, the study centre will be requested to validate the information on hospitalisation. If the information cannot be clarified, the higher value will be used for data analysis.

### Secondary outcomes

The following secondary outcomes will be analysed on the basis of data collected by study nurses during home visits at baseline and after 6 and 12 months:
Total number of medications, Drug Burden Index defined as the number of anticholinergic and sedative medications [16], prevalence of potentially inappropriate medications (PIMs) [35, 36], medication regimen complexity [37], and drug–drug interactionsWeakness measured by grip strength using a dynamometer (model SH5001; Saehan Corp., Masan, Republic of Korea); best of three attempts usedCognition: Two short cognitive subtests from the Consortium to Establish a Registry for Alzheimer’s Disease neuropsychological test battery, German version, with norms and reliable change indices recently derived from an older German GP sample [38, 39]:
◦ Episodic memory: word list learning (three trials immediate and one trial delayed recall); total administration time: maximum of 10 min plus 10-min interval and approximately 30 s for instruction◦ Executive function: semantic fluency (animal naming test) as a measure of combined verbal ability and executive control; administration time 1 min plus approximately 20 s for instructionDepressive disorder assessed by the Geriatric Depression Scale [40]Mobility measured by the Timed Up & Go Test [41]Health-related quality of life (EQ-5D-5L) will be assessed to facilitate calculation of quality-adjusted life-years (QALYs) for use in the economic analysis [42].Activities of daily living measured by the Barthel index [43]Weight (self-reported)Number of falls (self-reported)Use of emergency services

Detailed procedures of the measurements are listed in the schedule of enrolment, interventions, and assessments (Table 1).

**Table 1 Tab1:** Adapted SPIRIT schedule of enrolment, interventions, and assessments

	Study period						
	Enrolment	Baseline	Intervention				Close-out
Time point	**− t**_**1**_	**t**_**0**_			**t**_**1**_		**t**_**2**_
Month	− 3	0	1	3	6	9	12
Enrolment							
Eligibility screen	X						
Informed consent	X						
Allocation		X					
Interventions							
Intervention group (family conferences)			X	X		X	
Control group (care as usual)							
Assessments							
Hospitalisation rate (NHPP)					X		X
Medication (TNM, DBI, PIM)		X			X		X
Grip strength		X			X		X
Cognition (CERAD)		X			X		X
Depression (GDS)		X			X		X
Mobility (Timed Up & Go Test)		X			X		X
Health-related quality of life (EQ-5D-5L)		X			X		X
Activities of daily living		X			X		X
Weight		X			X		X
Number of falls		X			X		X
Use of emergency services		X			X		X

*Abbreviations: CERAD* Consortium to Establish a Registry for Alzheimer’s Disease, *DBI* Drug Burden Index, *GDS* Geriatric Depression Scale, *NHPP* number of hospitalisations per patient, *PIM* potentially inappropriate medications, *SPIRIT* Standard Protocol Items: Recommendations for Interventional Trials, *TNM* total number of medications

Participant retention and complete follow-up will be promoted via phone calls by the study nurses. For patients who drop out of the study, the following parameters are requested by the GPs: hospitalisations, cardiovascular events (e.g., stroke, myocardial infarction), mortality, and other adverse events (AEs).

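### The Drug Burden Index is scored as a plain count of drugs, so it cannot register dose reductions or unfinished tapers, although dose data for regular drugs are collected at the same visits

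*Protocol article*

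**What the plan says.** Under Secondary outcomes, the protocol article names the "Drug Burden Index defined as the number of anticholinergic and sedative medications", next to "Total number of medications" and several other medication measures. No dose term is attached to the index there or anywhere else in the article. The outcomes in this list are to be analysed from "data collected by study nurses during home visits at baseline and after 6 and 12 months".

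Under Measurements, "the study nurse will collect data on all medications used by the patient within the last week". The recorded items include the "content of the active substance, German national drug code, periodic or as needed" status and "dosage and frequency (for periodic medication"). Dosage and frequency are therefore tied to regularly taken drugs; none is listed for drugs taken as needed.

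Under Experimental intervention, GPs are trained in a "structured deprescribing protocol in case of a decision in favour of reducing the drug burden". The last of its five steps is to "implement a discontinuation regime and monitor patients closely". Family conferences are held at the start and after 3 and 9 months.

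**The concern.** The intervention sets out to lower drug burden, and this is the outcome whose name promises to measure it. Burden can fall in two ways: a drug is stopped, or it is continued at a lower dose. A count sees only the first. The Background section itself mentions tapering alongside withdrawal when it reviews earlier trials, with benzodiazepines among its examples, so the distinction is known to the authors.

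Timing adds to this. Conferences at months 3 and 9 precede the assessments at months 6 and 12 by three months each. A stepwise reduction agreed at one of them and not finished by the next visit scores the same as no action.

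What is at stake is the reading of this one outcome. A flat result could mean that exposure did not change, or that it changed without drugs being stopped. The stated definition cannot tell these apart, although for regular drugs the data to do so are in the database.

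**Working it through.** **Figures in the plan.** The article gives no mean, standard deviation or power for the Drug Burden Index, so there is no figure for it to reproduce. The Sample size section rests on hospitalisations only (0.75 versus 0.5, SD 1.0, 80% power, two-sided alpha 0.05). It reproduces:

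- Two-sample t test: 252.1, rounded up to 253 per group.
- Design effect: 1 + (5 − 1) × 0.05 = 1.2.
- Clustered total: 2 × 253 × 1.2 = 607.2, so 608 patients; 608 / 5 = 121.6, so 122 practices.
- Drop-out: 608 / 0.9 = 675.6, so 676 patients; 676 / 5 = 135.2, so 136 GPs.

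None of this involves the index.

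**The scoring rule.** Let d_i be the daily dose of drug i in the two classes, expressed as a multiple of a reference dose. The stated index is C = number of drugs with d_i > 0. If d_i falls but stays above 0, the change in C is 0.

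**Illustration.** Assume a patient on three such drugs, each at one reference dose. Two dose-weighted scores are shown for contrast only: a proportional one, P = Σ d_i, and a saturating one, S = Σ d_i / (d_i + 1). Neither is taken from the documents.

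| Change | Count C | Proportional P | Saturating S |
|---|---|---|---|
| Halve one of three | 3 → 3 | 3 → 2.5 | 1.5 → 1.333 |
| Halve all three | 3 → 3 | 3 → 1.5 | 1.5 → 1.0 |
| Stop one of three | 3 → 2 | 3 → 2 | 1.5 → 1.0 |

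The count registers the stop and misses both dose reductions. The two weighted scores register all three changes but rank them differently: halving all three is a larger change than stopping one under P, and an equal change under S. The form of the weighting therefore has to be fixed in advance.

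**Are the data there?** Strength, dosage and frequency together give a daily dose for each regularly taken drug at baseline, month 6 and month 12, the visits at which the index is scored. For as-needed drugs, strength is recorded but no dosage or frequency, so d_i is unknown.

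**How much is missed?** If a share p of the reductions in these classes present at a visit are dose reductions and not stops, the count misses that share p. The documents give no value or range for p.

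**The case against.** The strongest reply is that the count fits the plan's stated target. The Background section's secondary hypothesis concerns the number of inappropriate drugs prescribed, and the deprescribing steps end in discontinuation. A count records exactly that, and no passage sets dose reduction as a goal. This stands, and it confines the loss to doses lowered without a stop and to tapers still under way at a visit.

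It also rules out some stronger readings that a reader might infer:

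- *The comparison is biased towards no effect.* The between-group difference in the number of these drugs is estimated without bias by counting them. Leaving dose out means that a different quantity is estimated. Even the direction of what is missed is not established, since doses of continued drugs could also rise.
- *The index repeats the total drug count.* A count restricted to two drug classes shows something the total cannot. The Background section singles out psychotropic drugs as a group whose reduction can benefit patients.
- *A definite share of changes is lost.* Any percentage would be a guess.
- *The definition departs from the source it cites.* That source is not at hand, and the point does not need it.

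Two further replies carry some weight. As-needed drugs cannot be dose-weighted from the recorded data, whereas the count treats all drugs alike; this is a reason to keep the count. Other analyses, such as medication regimen complexity and the descriptive comparison of medication changes under Process evaluation, might pick up some dosing changes, but the article does not say whether they use dose.

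Finally, the article is condensed, and detailed scoring may sit in a full protocol or analysis plan. But it does not leave the scoring open: it states a rule. If a fuller document uses a dose-based formula, the published sentence disagrees with it and should be corrected.

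**Conclusion.** The point holds in a limited form. As defined, the Drug Burden Index registers stops and starts but no dose change, although dose is recorded for regular drugs at the same visits. The count is valid for what it counts; the outcome is insensitive to partial reductions in exposure. The per-patient effect is exact (a dose reduction contributes 0), but the effect on the trial result cannot be sized because the frequency of dose reductions and unfinished tapers is not given. It may be small.

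The conclusion rests on the article's own definition and its list of recorded items, and on the assumption that no unseen document overrides that definition. The primary endpoint, the sample size and the main conclusion of the trial are untouched. The change is worth making because it is cheap, not because the trial depends on it.

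**What to change.** Before outcome data are analysed:

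1. Define the Drug Burden Index as a dose-weighted sum over regularly taken anticholinergic and sedative drugs, using the strength, dosage and frequency already recorded. State the weighting formula, the list of drugs and the reference dose for each. The reference doses are scoring constants only and carry no treatment advice.
2. Keep the present measure as a separate secondary outcome under its own name, a count of anticholinergic and sedative drugs. It also covers as-needed drugs.
3. Add a sensitivity analysis for as-needed drugs, for example giving each a weight of zero and then the weight of one reference dose per day, to show how far the result depends on them.
4. State what is done when dosage or frequency is missing for a regular drug.

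The cost is wording, a reference-dose table and programming; no new data, visits or patients are needed. The drawbacks are that the reference doses must come from outside the documents, that as-needed drugs have no recorded dose and so rest on assumption, and that one more secondary outcome is reported. If the sponsor prefers not to weight by dose, renaming the outcome as a count would at least make clear what it measures, but the insensitivity to dose would remain.
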